### Comparing mortality rates of investigational arms to the control arm up to 29 days after randomization

Boschloo’s test will be used to evaluate 15-day and 29-day clinical status and SARS-CoV-2 viral status in the manner proscribed for the primary and secondary analysis.

Table: Sample size, number (%) with 15-day 7-point ordinal scale clinical outcome status, number (%) missing 15-day 7-point ordinal scale clinical outcome status and 15-day SARS-CoV-2 viral status. *P*-values from Boschloo’s test comparing each arm to control.

Table: Sample size, number (%) with 29-day 7-point ordinal scale clinical outcome status, number (%) missing 29-day 7-point ordinal scale clinical outcome status and 29-day SARS-CoV-2 viral status. *P*-values from Boschloo’s test comparing each arm to control.

#### Comparing time to meeting criteria for successful discharge from the COVID-19 treatment centre between participants receiving investigational therapeutics, relative to the control arm

Differences in median days to becoming eligible for discharge will be tested using the Wilcoxon rank-sum test, imputing deaths prior to day 28 as the worst rank, with earlier deaths having a worse rank than later deaths.Discharge decisions may not always be based on objective clinical data. For these reasons, time to meeting criteria for successful discharge will be analysed rather than time to actual discharge.We will tabulate the sample size, number (%) who became eligible for discharge within 29 days, mean, median and standard deviation of days to discharge eligibility among those for whom the endpoint is available. *P*-values for test of medians using Wilcoxon rank-sum test.Side-by-side plots and boxplots of time to meeting criteria for successful discharge by arm, separately for symptomatic and asymptomatic cases, will be prepared.

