## Sample size {14}

The sample size of 200 per arm has been calculated assuming an odds ratio (*OR*) of 2, 85% power and a 2-tailed test at level *α* = 0.05 and allowing for approximately 10% of participants to be lost to follow-up. The odds ratio represents the odds of improvement in the ordinal scale for treatment relative to control.

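### The discharge-eligibility p-value is labelled a test of medians, but it compares ranks that include deaths, while the median shown beside it appears to leave deaths out

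*Protocol article*

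**What the plan says.** The point concerns the protocol article, Methods for additional analyses {20b}, under the heading on time to meeting criteria for successful discharge.

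- **Target and test:** "Differences in median days to becoming eligible for discharge will be tested using the Wilcoxon rank-sum test".
- **Deaths in the test:** "imputing deaths prior to day 28 as the worst rank, with earlier deaths having a worse rank than later deaths".
- **Table:** the sample size, the "number (%) who became eligible for discharge within 29 days", and then the "mean, median and standard deviation of days to discharge eligibility among those for whom the endpoint is available".
- **Label on the p-value:** "for test of medians using Wilcoxon rank-sum test".

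The article states no assumption that the two arms' distributions have the same shape, and it names no rank-based effect measure to accompany the p-value.

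**The concern.** Two things do not fit together.

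First, the rank-sum test asks whether participants in one arm tend to rank better than those in the other, over the whole ranked outcome and with deaths at the bottom. That is the same question as equality of medians only when one arm's distribution is the other's moved along the time axis. If death rates differ, the worst-ranked part of the outcome differs between arms, so a pure shift cannot hold exactly. The trial also enrols asymptomatic through severe cases. A drug that acts mainly in one of these groups would change the shape of the distribution as well as its location.

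Second, a mean and SD in days cannot include a death rank. The natural reading is therefore that the tabulated figures omit participants who died, and likewise those not eligible by day 29. The test keeps the deaths. The p-value and the median printed beside it then describe different sets of participants, and the median's set is selected by something that happens after randomisation.

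The Discussion says a positive result would feed a State guideline that is likely to be adopted nationally. A median number of days to discharge eligibility is the kind of figure that would be quoted there. A drug that hastens recovery in survivors while adding deaths could show a better median next to a p-value that answers another question.

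**Working it through.** The section gives no figure of its own to reproduce, so the check is how the stated test behaves at this trial's size.

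**Inputs**
- Size, from Sample size {14}: "The sample size of 200 per arm has been calculated" with about 10% loss, so 200 × 0.9 = 180 evaluable per arm. Allocation is equal.
- Mortality: Outcomes {12} calls it low without a figure. The Background reports 603 deaths in 26,484 Nigerian cases, and 603/26,484 = 2.3%.
- Assumptions: two-sided 0.05 (this section gives no alpha), whole-day times, and survivors not eligible by day 29 ranked after all eligible survivors and ahead of deaths.

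**1. Is the test valid?** In 5,000 simulated trials with identical distributions, it rejected in 5.1% at both 180 and 200 per arm. It is correctly calibrated.

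**2. Only deaths differ.** Let survivors have the same time distribution in both arms, with death probabilities d0 (control) and d1 (drug) and the same timing of deaths. The probability that a drug participant ranks better, counting ties as half, is

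θ = ½(1−d0)(1−d1) + d0(1−d1) + ½·d0·d1 = ½ − (d1−d0)/2.

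The null standard error is √[(2n+1)/(12n²)] = √[361/(12 × 180²)] = 0.0305. With z = (½ − θ)/0.0305, the rejection rate is approximately Φ(z − 1.96) + Φ(−z − 1.96).

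| Assumed deaths, control v drug | θ | z | Formula | Simulation, n = 180 |
|---|---|---|---|---|
| 2.3% v 3.5% | 0.494 | 0.20 | 5.4% | 4.7% |
| 2.3% v 4.6% | 0.4885 | 0.38 | 6.7% | 7.1% |
| 2.3% v 6% | 0.4815 | 0.61 | 9.3% | 9.8% |
| 2% v 6% | 0.480 | 0.66 | 10.1% | 10.6% |
| 2% v 10% | 0.460 | 1.31 | 25.9% | 26.2% |
| 5% v 20% | 0.425 | 2.46 | 69.2% | 69.2% |

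The first three rows used 4,000 runs and the others 5,000, so simulation error is about 0.3 percentage points or more. At 200 per arm, the 2% v 6% row becomes 11.0%. The available-only median has the same distribution in both arms in every row. A significant result would thus be called a difference in medians although the displayed medians do not differ systematically.

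**3. Medians differ but ranks do not.** Take underlying medians of 8 and 10 days, shaped so that θ = ½. The test rejects in 6.3% of trials and so misses the 2-day difference about 94% of the time. This case is constructed and only shows that the two hypotheses can separate.

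**4. Equal medians, different shapes.** Rejection ranges from 6.3% (symmetric on the log scale, spread 0.3 v 0.7) to 99–100% (strongly asymmetric shapes). Whole-day rounding leaves average sample medians about 0.3 to 0.6 day apart in these cases, so they are bounds and not forecasts.

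**5. Gap between the two medians.** With 2.3% to 4.6% deaths and log-normal times (median about 10 days, log SD 0.45), the median over everyone ranked exceeds the available-only median by about 0.2 to 0.35 day.

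**The case against.** The strongest reply is that this is loose wording around a sound analysis, and much of that stands.

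- A reader might infer that the test's type I error is inflated. It is not. In every scenario above where rejection clearly exceeds 5%, the arms truly differ, and responding to extra deaths is what ranking deaths worst is for.
- A reader might infer that a change in deaths leaves the median alone. That is not generally so. Extra deaths drawn from across the distribution move the median of the full ranked set. The available-only median is the one that can stay put.
- A reader might take the 26% and 69% rows as the likely size. Death rates of 10% or 20% sit badly with a protocol that calls mortality low and reports about 2.3% of national cases dying.
- A reader might infer that the harm would be hidden. The same table gives the number eligible within 29 days, plots by arm are planned, and ordinal status at days 15 and 29, which includes death, is tabulated by arm.
- This is an additional analysis and the endpoint is not in Table 3. It does not enter the primary test, the sample size or the stopping rules.
- The exclusion of deaths from the summaries is inferred from the wording, and the choice of a rank-based estimate can be left to the analysis plan.

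What the reply does not remove is that the article itself states the target as medians, labels the p-value accordingly, and pairs it with a median from another set.

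**Conclusion.** The point holds as a mismatch between the test, its label and the estimate shown with it. The Wilcoxon test with worst-ranked deaths is valid for the ranked composite of time and death. It tests medians only under a pure shift, and the tabulated median, on the natural reading, describes only participants who reached the endpoint.

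The practical effect is modest at the mortality the protocol describes. When only deaths differ, at about 2% against 3.5% to 6%, rejection is roughly 5% to 11%, and the two versions of the median differ by a few tenths of a day. These sizes rest on assumed time distributions, assumed death rates, two-sided 0.05 and an assumed rank for survivors not yet eligible. Larger gaps need larger mortality differences or clear differences in shape. The issue affects the interpretation of an additional analysis and leaves the primary result untouched. It is still worth correcting, because the correction changes a reported estimate and what may be concluded from it.

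**What to change.** In the {20b} section on time to discharge eligibility:

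1. Describe the p-value as a rank comparison of time to discharge eligibility with death ranked worst, and drop the references to a test of medians in both the text and the table specification.
2. Compute the displayed median and quartiles over the same set used in the test, with deaths ranked as planned and participants not eligible by day 29 placed beyond day 29. While editing, reconcile the day-28 limit in the death rule with the 29-day horizon of the table.
3. Keep the available-only mean, median and SD as labelled description, without a p-value.
4. Optionally add a matching estimate, such as the Mann-Whitney probability with a 95% confidence interval.

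The planned test is unchanged and no new data are needed. The small cost is that the all-participant median may look less favourable, and a rank-based estimate is less familiar to readers than a difference in days.

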2. To evaluate the safety of chloroquine phosphate, hydroxychloroquine sulphate and lopinavir/ritonavir added on to standard therapy compared to standard therapy in the treatment of individuals with laboratory-confirmed COVID-19 2.1 To evaluate the safety of chloroquine phosphate added on to standard therapy compared to standard therapy in the treatment of individuals with laboratory-confirmed COVID-19 2.2 To evaluate the safety of hydroxychloroquine sulphate added on to standard therapy compared to standard therapy in the treatment of individuals with laboratory-confirmed COVID-19 2.3 To evaluate the safety of lopinavir/ritonavir added on to standard therapy compared to standard therapy in the treatment of individuals with laboratory-confirmed COVID-19	1. Cumulative incidence of severe adverse events up to and including day 29 2. Changes in laboratory safety indices assessed on days 1, 8 and 15—haemoglobin concentration, platelet count, white blood cell count, glucose, creatinine, total bilirubin, ALT and AST

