#### Statistical methods for analyzing secondary outcomes

The following analyses will be performed for the comparison of each experimental arm to the placebo arm when full enrolment has been achieved. For these analyses, the alpha level used is that of the analysis for the primary outcome when full enrolment has been achieved.
The Mantel-Haenszel odds ratio estimator and test statistic will be applied to the strata defined by clinical signs and symptoms (asymptomatic versus symptomatic).Differences in time-to-event endpoints (e.g. time to negative SARS-CoV-2 status) by treatment will be summarized with Kaplan-Meier curves and 95% confidence bounds.Change in ordinal scale at specific time points will be summarized by proportions (e.g. proportion who have a 1-, 2-, 3- or 4-point improvement or worsening).Duration of event (e.g. duration of mechanical ventilation) will be summarized according to median days with quartiles.Incidence data (e.g. incidence of new oxygen use) will be summarized as a percent with 95% confidence intervals.Categorical data (e.g. 28-day mortality or ordinal scale by day) will be summarized according to proportions with confidence intervals on the difference or odds ratios for a binary or multiple category scale, respectively.Logistic regression analyses will be undertaken to assess the effect of covariates on outcomes.

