### Methods in analysis to handle protocol non-adherence and any statistical methods to handle missing data {20c}

The analysis population will be based on intention-to-treat. No account will be taken for protocol non-adherence.

For missing data, patterns of missing data will be explored in the primary and secondary outcomes and reported. If required, multiple imputation statistical technique will be used assuming the mechanism of missing data is missing at random (MAR).

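### The discharge-eligibility analysis ranks deaths only before day 28 but counts eligibility to 29 days, gives no rank to survivors who are still ineligible, and reports medians on a different set of participants from its test

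*Protocol article*

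**What the plan says.** All references are to the protocol article. The analysis is one of the additional analyses under item {20b}, in the section on time to meeting criteria for successful discharge.

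- **Test and rank rule.** Days to becoming eligible for discharge are compared with a Wilcoxon rank-sum test, "imputing deaths prior to day 28 as the worst rank, with earlier deaths having a worse rank than later deaths". No other outcome is given a rank.
- **Horizon of the table.** The same section tabulates the "number (%) who became eligible for discharge within 29 days".
- **Who is summarized.** The mean, median and standard deviation are given "among those for whom the endpoint is available". The accompanying P-value is described as a test of medians.
- **Horizons elsewhere.** Table 3 in Outcomes {12} lists "Cumulative incidence of severe adverse events up to and including day 29" and the ordinal scale on day 29. A neighbouring section of {20b} is headed "Comparing mortality rates of investigational arms to the control arm up to 29 days after randomization". The section on secondary outcomes, by contrast, mentions 28-day mortality as an example.
- **General rules.** Under {20c}, "The analysis population will be based on intention-to-treat", and multiple imputation under missing at random may be used if required.

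**The concern.** A worst-rank analysis works when every randomized participant with a known outcome has a place in the ordering. Here the ordering is incomplete in two places: deaths at the end of the window, and survivors who have not met the criteria when the window closes. Both are observed failures, not missing data. If whoever runs the analysis leaves them out, or lets the imputation model give them an eligibility time, the test compares speed of recovery only among those who recovered or died early. That conditions on an outcome after randomization and departs from the stated intention-to-treat principle.

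The summary has a separate fault that does not depend on any gap in the rule. The P-value counts deaths as worst ranks, while the medians beside it leave out everyone without an observed time. A reader would take the two as describing the same comparison.

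**Working it through.** **1. The two horizons.** Table 4 labels baseline as day 1, so study day 29 is 28 days after baseline. The possible readings are:

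| Meaning of day 28 in the rank rule | Deaths given a worst rank | Deaths on or before study day 29 with no stated rank |
|---|---|---|
| Study day 28 | Study days 1–27 | Study days 28 and 29 |
| 28 days after baseline (study day 29) | Study days 1–28 | Study day 29 |

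If the 29 days are instead counted from randomization on day 1, the window ends on study day 30 and each gap is one day wider. The rule says prior to day 28, so no reading closes the gap.

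**2. Who has a rank.**

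| Participant | Stated rank |
|---|---|
| Eligible within the window | Observed time |
| Dead before day 28 | Worst, earlier deaths worse |
| Dead at the end of the window, not yet eligible | None stated |
| Alive at day 29, not yet eligible | None stated |

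The fourth row can occur: the ordinal scale is scored on day 29 and includes hospitalized and ventilated categories.

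**3. Size, if ineligible survivors were dropped.** The article gives no failure rates and no power for this analysis, so there is no figure of the plan to reproduce. The planned 200 per arm, set for the primary endpoint in Sample size {14}, supplies n. All failure rates below are assumptions.

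Suppose times are identical among those who become eligible and a fraction f1 versus f2 never does. If these participants are ranked as failures, then approximately

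P(worse) = 0.5 + (f1 − f2)/2, with SE = √[(n1 + n2 + 1)/(12·n1·n2)] = √[401/(12 × 200 × 200)] = 0.0289.

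For 5% versus 2%: P(worse) = 0.515 and z = 0.015/0.0289 = 0.52. The two-sided rejection rate is Φ(0.52 − 1.96) + Φ(−0.52 − 1.96) = 0.075 + 0.007, about 8%. If they are dropped, the arms are identical and the rate is 5%.

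For 10% versus 5%: z = 0.025/0.0289 = 0.87, giving about 14% against 5%.

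A simulation (200 per arm, 4,000 runs, 2% ranked deaths per arm, lognormal times with median 12 days among the eligible) gave these rejection rates:

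| Never eligible, arm A vs arm B | Ranked as failures | Dropped |
|---|---|---|
| 5% vs 5% | 5% | 5% |
| 15% vs 5% | 40% | 5% |
| 20% vs 5% | 72% | 5% |
| 20% vs 10% | 40% | 6% |
| 30% vs 15% | 74% | 5% |

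The formula agrees for 15% versus 5%: z = 0.05/0.0289 = 1.73, giving about 41%. The large contrasts need failure rates that nothing in the article supports. They show that dropping makes the test blind to such differences, not that they are expected here.

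**4. Medians.** If a fraction F of an arm fails (dead or never eligible), the median over all participants is the 0.5/(1 − F) quantile of times among the eligible. With 2% deaths in each arm:

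- 5% versus 2% never eligible: 0.5/0.93 = 0.538 and 0.5/0.96 = 0.521, so the medians sit at the 53.8th and 52.1st percentiles.
- 15% versus 5%: 0.5/0.83 = 0.602 and 0.5/0.93 = 0.538.

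The summary restricted to those with an observed time reports the 50th percentile in every arm, whatever F is.

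**The case against.** The strongest reply is that the survivor part rests on silence. A reader might infer that ineligible survivors are excluded from the Wilcoxon test. The article does not say so. The phrase "among those for whom the endpoint is available" qualifies the descriptive statistics, not the test population; the stated population is intention-to-treat; and an analysis plan not shown could rank these survivors without changing the method. That stands, and for this reason the point is put conditionally.

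A reader might also infer that the omission favours the drug. It does so only if failures are more common in the drug arm; with the rates reversed it works against the drug. The article supports neither direction.

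The mismatch between 28 and 29 may be a day-count slip, and it touches very few people: asymptomatic and mild cases are enrolled, and Outcomes {12} refers to a low mortality rate. That is fair as to size. It does not remove the mismatch, since prior to day 28 leaves at least the last day uncovered on every reading.

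Failures would not be hidden altogether. The number eligible within 29 days is tabulated, and the 29-day ordinal scale is tested separately. This limits the harm but does not align the P-value with the medians. That fault, like the cut-off, lies in what the article states, so neither can be put down to detail left for the analysis plan.

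**Conclusion.** The point holds in a limited form. Two faults are in the text: a death cut-off that stops short of the analysis window, and a mean, median and standard deviation that describe a different set of participants from the P-value. A third is an incomplete rule: survivors not eligible by day 29 have no stated rank, and the general missing-at-random fallback would be wrong for them because their outcome is known. It cannot be concluded that they will be excluded, nor that any bias favours the drug.

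The effect is probably small. At 5% versus 2% never eligible the rejection rate moves from about 8% to 5%; larger effects need failure rates of 15% or more in one arm, which are assumptions. Time to discharge eligibility is an additional analysis and is not itself listed in Table 3. The primary endpoint, the sample size and the interim efficacy monitoring are untouched. It is worth correcting because the change is cheap and settles, before unblinding, who counts as a failure.

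**What to change.** Amend the discharge-eligibility section of {20b} as follows:

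1. Use one fixed horizon, study day 29, for both deaths and eligibility. Do not use the date of the final visit, whose ±3-day window would let the horizon vary from day 26 to day 32.
2. Rank all deaths through study day 29 worst, with earlier deaths worse than later ones.
3. Rank survivors not eligible by study day 29 as tied, worse than every eligible participant and better than every death. Reserve the missing-data rule in {20c} for participants whose status is truly unknown.
4. Report the median for all randomized participants on this same ranking, next to the P-value. Keep the summary among those who became eligible as descriptive only.

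The cost is a few lines of wording. Death and hospitalization at day 29 are already captured by the day-29 ordinal score. That score does not itself show whether discharge criteria were met, so the eligibility date must come from the record this analysis already needs; participants seen on days 26 to 28 need their status confirmed to day 29. The reported medians may be slightly longer.

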#### Pharmacokinetic assessments of investigational agents

In general, pharmacokinetic measurements often involve processing (e.g. centrifugation) and testing of blood specimens with techniques or equipment not routinely available or safely performed in most point-of-care laboratory set-ups. These considerations, coupled with limitations on storage, transport and analytical processing of infectious samples falling under Select Agent regulations, could limit these explorations outside the context of a high containment laboratory such as a domestic BSL-4 laboratory in Lagos State.

When possible, pharmacokinetic assessments will include summaries of mean and 95% confidence intervals for parameters such as the area under the curve (AUC) of concentration versus time, Cmax and Cmin, clearance time, volume of distribution, half-life and bioavailability.

### Methods in analysis to handle protocol non-adherence and any statistical methods to handle missing data {20c}

The analysis population will be based on intention-to-treat. No account will be taken for protocol non-adherence.

For missing data, patterns of missing data will be explored in the primary and secondary outcomes and reported. If required, multiple imputation statistical technique will be used assuming the mechanism of missing data is missing at random (MAR).

